# Education of Patients With Atrial Fibrillation and Evaluation of the Efficacy of a Mobile Virtual Patient Environment: Protocol for a Multicenter Pseudorandomized Controlled Trial

**DOI:** 10.2196/45946

**Published:** 2024-01-23

**Keywords:** atrial fibrillation, virtual patient, scenario based learning, technology enhanced learning, mHealth, mobile health, patient engagement, patient education, cardiac arrhythmia, mortality, mobile application, mobile app, health education, randomized control trial, cardiology, cardiac, heart, Greece, Ukraine, Kazakhstan, clinical decision support systems, CDSS, virtual patient scenario, myocardial infarction, arrhythmia, stroke

## Abstract

**Background:**

Atrial fibrillation (AF) is the most common sustained cardiac arrhythmia and is a leading cause of mortality and morbidity. Patient knowledge about AF and its management is paramount but often limited. Patients need to be appropriately informed about treatment options, medicinal adherence, and potential consequences of nonadherence, while also understanding treatment goals and expectations from it. Mobile health apps have experienced an explosion both in their availability and acceptance as “soft interventions” for patient engagement and education; however, the prolific nature of such solutions revealed a gap in the evidence base regarding their efficacy and impact. Virtual patients (VPs), interactive computer simulations, have been used as learning activities in modern health care education. VPs demonstrably improved cognitive and behavioral skills; hence, they have been effectively implemented across undergraduate and postgraduate curricula. However, their application in patient education has been rather limited so far.

**Objective:**

This work aims to implement and evaluate the efficacy of a mobile-deployed VP regimen for the education and engagement of patients with AF on crucial topics regarding their condition. A mobile VP app is being developed with the goal of each VP being a simple scenario with a set goal and very specific messages and will be subsequently attempted and evaluated.

**Methods:**

A mobile VP player app is being developed so as to be used for the design of 3 educational scenarios for AF management. A pseudorandomized controlled trial for the efficacy of VPs is planned to be executed at 3 sites in Greece, Ukraine, and Kazakhstan for patients with AF. The Welch *t* test will be used to demonstrate the performance of patients’ evaluation of the VP experience.

**Results:**

Our study is at the development stage. A preliminary study regarding the system’s development and feasibility was initiated in December 2022. The results of our study are expected to be available in 2024 or when the needed sample size is achieved.

**Conclusions:**

This study aims to evaluate and demonstrate the first significant evidence for the value of VP resources in outreach and training endeavors for empowering and patients with AF and fostering healthy habits among them.

**International Registered Report Identifier (IRRID):**

PRR1-10.2196/45946

## Introduction

### Impact of Atrial Fibrillation and Non–Vitamin K Oral Anticoagulants and the Role of Integrated Management

Atrial fibrillation (AF) is the most frequent long-term cardiac arrhythmia in adults, presenting a considerable burden on patients, health care systems, societal health, and the global health economy [1]. Because AF is associated with significant morbidity and mortality, numerous research efforts and resources are being directed toward gaining more detailed information about the mechanisms underlying AF, its natural course, and effective treatments, and new evidence is being generated and published on a regular basis [2].

The current estimated prevalence of AF is between 2% and 4% [3], with a 2.3-fold increase projected due to the general population's increased longevity and the intensive search for AF [4]. AF is a well-known risk factor for thrombus development in the left atrium and eventual embolism on the left side. AF raises the risk of stroke by 5 folds, but the risk varies depending on the presence of stroke risk factors or modifiers [2]. Oral anticoagulants (OAC) are the cornerstone of AF treatment. Vitamin K antagonist (VKA) medication (mainly warfarin) lowers the risk of stroke and death by 64% and 26%, respectively, when compared to control or placebo [5]. Non–vitamin K oral OACs (NOACs) have outperformed VKAs in most therapeutic circumstances. NOAC medications do not have the practical constraints of VKAs, such as a small therapeutic window, interactions with food and other treatments, and the need to monitor coagulation levels. In 4 large randomized controlled trials (RCTs) with patients with AF, NOACs were compared to warfarin [6-9]. They were demonstrated to be at least noninferior to VKA therapy for the prevention of stroke or recurrent venous thromboembolism and were associated with a lower risk of bleeding. In a meta-analysis of these RCTs, NOACs were associated with a 19% significant reduction in the risk of stroke or systemic embolism, a 51% reduction in the risk of hemorrhagic stroke, and a similar reduction in the risk of ischemic stroke compared to VKAs. NOACs are also associated with a 10% reduction in all-cause mortality [10].

To provide optimal medical treatment to patients with AF, integrated management necessitates a patient-individualized care route. Treatment choices should be reviewed and a management plan agreed upon with health care experts in this patient-centered approach [11]. Treatment is liable to alter over time as new symptoms, risk factors, disease progression, and novel medicines emerge. To prevent stroke and improve symptoms, it is critical to consider optimizing resource usage. The initial stage in shared decision-making should be to investigate the patients' preferences [12]. The importance of stroke prevention and rhythm control among patients, as well as the corresponding risks of death, stroke, and significant bleeding, should be properly appraised for shared decision-making.

Patients’ awareness of AF and its management is sometimes restricted, especially when first diagnosed, because the majority of treatment decisions must be addressed and made. Furthermore, controlling patients' expectations of treatment goals, as well as ensuring that patients are correctly informed about treatment options, how to better adhere to therapy, and potential repercussions of nonadherence, are critical to increase adherence [2]. Thorough education of physicians on these approaches, as well as correct adherence and active engagement of the patient in the treatment process, are critical to the success of each treatment plan. Soft health interventions for education and empowerment of both clinicians and patients are critical in this environment.

### Education and Other Soft Interventions Involving Mobile Health Apps in Cardiology

There has been an explosion of mobile health (mHealth) apps during the previous decade, with an estimated 3.7 billion downloads globally between 2013 and 2017 [13], many of which are intended for AF. A 2020 systematic review revealed around 11,152 articles related to mHealth apps for AF but only included 9 studies with real outcomes about mHealth therapies for AF in its results synthesis [14]. This indicates the prevalence of such solutions, as well as the dearth of data on their efficacy and impact. Only a few apps have been evaluated formally [15-17]. It should be emphasized that there are few apps that are specifically intended for patients. There are numerous informative apps that patients can use; however, a preferred option would be the development of a specific app for the treatment of a given ailment in order to help afflicted individuals in a more appropriate way [18].

Clinical decision support systems that digitize and provide evidence-based recommendations, therapeutic pathways, and algorithms to facilitate individualized, timely, and evidence-based treatment could be a valuable aid in the holistic management of AF. To improve patient-integrated AF management [19], the MobiGuide project [20] and numerous applications have been deployed. The European Society of Cardiology–Characterizing Atrial fibrillation by Translating its Causes into Health Modifiers in the Elderly Consortium partnership offers a smartphone or tablet app for patients with AF; however, it has yet to be tested prospectively [21]. Contradictory findings highlight the need for more properly designed trials, including evaluation of the intervention's influence on clinical outcomes [22].

As a result, the scope and impact of mHealth apps for AF, as well as the level of patient and health care professional (HCP) engagement and acceptability, are currently unknown. HCP engagement refers to information sharing between the patient and provider, shared responsibilities in decision-making processes, and support of patients’ choices and acceptability to a degree to which an intervention is approved by most HCPs. Given both patients and HCPs may easily use these applications, it is critical to understand their scope and content and their acceptability among users, and to investigate the purpose and results of app adoption and usage.

### Virtual Patients in Health Care Education

Virtual patients (VPs)—interactive computer-based clinical scenarios for the purpose of medical training, education, or assessment—have been increasingly used as learning activities in current health care education, particularly in teaching decision-making through scenarios [23]. Because VPs can enhance cognitive and behavioral skills, they have been successfully incorporated in undergraduate and postgraduate curricula [24]. With the rising use of VPs, there are opportunities for pedagogical synergies to allow trainees of diverse categories to practice in realistic and safe learning contexts [25]. The key characteristics of VP systems are that they enable repetitive and intentional practice by any student, regardless of time or physical location, and that mistakes are not fatal. These opportunities provided by VPs in current medical education, combined with positive evaluation results from various studies demonstrating that they may improve cognitive and behavioral skills better than traditional methods [24], have resulted in a widespread trend toward VP creation and use among academic institutions [26]. Furthermore, VPs enable the production and usage of more game-based educational content, which provides the student more exploratory flexibility and provides a different area for case-based content in current medical education.

The widespread adoption of these digital technologies, not only in medical student education but also in the health care community in general and in the patient community, has undoubtedly been limited thus far, but it has the potential to educate and psychologically support high-risk patients and vulnerable populations in these new and unprecedented circumstances. Because numerous academic institutions have the VP resources and expertise in their execution, such effective educational content might be simply repurposed in a more patient-centered format and be used more widely by the patient community as an educational aid.

### Study Aim and Objectives

In this technological setting, we propose the development of a holistic approach to patient engagement and education based on the fundamentals of AF. The DEEP-RAFT (Doctors’ Education, Empowerment of Patients, Regarding Atrial Fibrillation and Venous Thromboembolism) project would generate a suite of educational and informational interventions along an axis created by 2 poles: digital content cocreation and evidence-based educational impact. This effort will be based on a suite of digital teaching resources, in the form of VPs, co-designed by continuous and immediate involvement of health care specialists, health care policy influencers, and patients. This strategy seeks, first and foremost, to develop materials that are more patient-centered and address realistic problems relevant to the health care systems involved in the project. The focus of this effort is on the second topic, evidence-based educational impact, which attempts to demonstrate the educational efficacy and acceptance of the generated resources as they may be used in a diverse but targeted set of education and outreach activities.

In practice, a mobile app for natively deploying VPs on mobile devices is developed, along with a list of relevant VPs. In the following parts, we will provide these concrete and intangible tools and approaches to contextualize the protocol that is described below.

## Methods

### Study Design

This is a 2-arm, parallel-group pseudorandomized controlled trial that will be performed at 3 sites—Greece, Ukraine, and Kazakhstan—and will include the evaluation of the educational VP interventions. This will be conducted in 2 axes that correspond to the primary outcomes of the study. The first axis aims to determine the efficacy of the educational VP interventions, while the other will involve assessing the acceptance and opinions of the participants about the VP modality for education and information purposes. Correspondingly, the primary outcomes of the study include the efficacy and the acceptance of the VP interventions, and the secondary outcomes include the opinions of the participants about the VP modality for education and information purposes. The aims of the study are summarized in the following research question: are patients with AF better educated about their post–acute phase lifestyle changes and needs by using mobile virtual scenarios compared to conventional patient education methods?

Α prepilot arm of the study will be initially conducted in Greece and will consist of hospitalized patients due to AF episodes, all of which should complete a short quiz. From among the patients who complete the quiz, half of the patients will be randomly allocated to the control (normal clinical information) cohort, while the other half will be informed with the help of VP vignettes.

After the prepilot arm, the pseudorandomized controlled trial will be conducted multicentrically. The same process, as in the prepilot arm, will be followed for recruiting the core sample, exploring the efficacy and impact of VPs in educating patients with AF. Since this trial will have been conducted during the COVID-19 pandemic, all national and international health and safety protocols will be followed.

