### The VPs

Three scenarios will be explored by the participating medical teams. All will be focused on the patients, since these are the target group of the VPs. A tabulated outline of these scenarios is presented in Table 1. The first scenario should be dealing with a chronic case of AF, including guidance for good medication adherence, systematic medical appointments, and correct communication. The second scenario would be about detecting early onset and prevention of paroxysmic AF. The third scenario will deal with a case of AF that involves lifestyle-compounding factors to the disease (smoking, drinking, and unhealthy eating), as well as more heavy complications that are significantly more probable in such cases.

**Table 1 table1:** Outline of suggested scenarios and educational objectives of virtual patients.

Scenario theme	Educational objectives (after encountering this educational virtual scenario vignette, the patient will be able to…)
Chronic case of AF^a^	Identify correct medication adherence practices Identify the correct frequency regimen of doctors’ appointments Identify correct dietary restrictions
Early-onset and paroxysmic AF	Identify initial onset of symptoms of AF Identify timely medical consultation practices Recognize the correct medicinal adherence procedure for the condition Identify the correct exercise intensity to manage the condition
AF with lifestyle- compounding factors to the disease (smoking, drinking, and unhealthy eating)	All educational objectives of “Chronic case of AF” Identify risks of high-impact complications Identify best practices for recovering from missed doses of medical treatment

^a^AF: atrial fibrillation.

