Iterative brainstorming between the medical experts of all study centers will produce the detailed VP scenarios in the mobile digital platform (for details, refer to the previous section, *The Technical Architecture of the Mobile App*). After an internal review of these scenarios by the multinational expert panel, a selection would be made for the final case to be used. In that context, the team will choose to simply use 1 scenario in the multicenter multinational cohort trials. The most appropriate scenario would have the following characteristics: (1) it should be the most relevant—a significantly larger proportion of patients should be targeted; (2) it should be the most clinically impactful—it is important and useful for patients with AF to be aware of AF complications; and (3) it should be the most educationally important—both patients who fall within the parameters of the described case and those who do not would benefit from information and preventative knowledge of the impact of AF.

An acceptance rate of 75% by medical experts for each criterion for each scenario should be reached to be eligible for recruitment. Moreover, this patient education intervention will be based on techniques from the behavior change technique taxonomy—an international consensus for the reporting of behavior change interventions [28].

After this selection, a process of localization and adaptation to the specifics of each center (Greece, Ukraine, and Kazakhstan) would be conducted.

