### Evaluation Design

#### Evaluation Instruments

For educational efficacy, a multiple-choice questionnaire (MCQ) for knowledge retention will be used (Textbox 2). The choice of questions was based on the European Society of Cardiology’s *Guidelines for Management of Atrial Fibrillation* [29]. This instrument will be translated for all participating centers in Greece, Ukraine, and Kazakhstan. The translation and evaluation of the translation will be performed by teams of bilingual experts. The instrument in its original version will be provided to bilingual persons in alternating language order and will be assessed accordingly. Scoring each questionnaire follows a simple process of allocating a numerical score equal to the number of choices in the MCQ to weigh each response for randomly selecting the correct question. For example, a question that has 4 possible responses in the MCQ will be scored 4 points if answered correctly, while a question that has 5 possible answers will be scored with 5 points if correctly answered.

Questionnaire for knowledge retention on atrial fibrillation (the asterisk indicates the correct answer).

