### Limitations

The study’s core limitation lies with the knowledge retention questionnaire. This is not a validated instrument. While we were aware of a formal validated instrument (the Jessa Atrial fibrillation Knowledge Questionnaire [40]), the knowledge spectrum that it covers is far wider than what our VP vignette may cover. Given that verbal and printed conventional information covers all relevant material, while our VP may cover specific critical topics related to AF, using a wide instrument such as the Jessa Atrial fibrillation Knowledge Questionnaire would run the risk to evaluate knowledge retention gaps that the VP vignette cannot cover. While a counterargument can be made that we are thus narrowing the evaluation scope to the strong points of our VP resource, the concise focus of the VP vignette is itself an argument for implementing it as a more effective educational tool in personalized and focused endeavors for patient empowerment. As a follow through too, we aim to address the second weakness of our study, which is the lack of a qualitative exploration about the acceptance of patients regarding the electronic medium of mobile devices and the modality of VPs in comparison to other existing modalities such as video demonstration or even gamified virtual environments.

Even given these limitations, however, this study can provide evidence for the comparatively better efficacy of the VP modality in mobile media for impactful and effective information for and empowerment of patients with AF. This study would be the first evidence-based step to initiate this process toward better informing and subsequent empowerment of patients with regard to the management of their disease.

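### The research question asks about lifestyle changes and needs, but no keyed answer in the ten-item knowledge quiz concerns a lifestyle change, so the efficacy outcome leaves the lifestyle part of the question unmeasured

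*Protocol article*

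**What the plan says.** Under Study Design, the aims are condensed into one research question. It asks whether patients come away knowing more, and its subject and comparison read "phase lifestyle changes and needs by using mobile virtual scenarios compared to conventional patient education methods" (the phase meant is the post-acute one). The same section says that "the primary outcomes of the study include the efficacy and the acceptance of the VP interventions".

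Evaluation Instruments names one tool for efficacy: "For educational efficacy, a multiple-choice questionnaire (MCQ) for knowledge retention will be used". On the origin of its items it says "The choice of questions was based on the European Society of Cardiology’s" guideline on AF management. Each item is weighted by its number of options; for example, "a question that has 4 possible responses in the MCQ will be scored 4 points if answered correctly". Textbox 2 prints all ten items with their keys.

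The VPs section outlines three suggested scenarios. Each has at least one lifestyle objective in Table 1: diet in the chronic scenario, exercise intensity in the early-onset scenario, and diet again in the third, which inherits all the chronic objectives and has smoking, alcohol and unhealthy eating as its theme. Other objectives are medical, such as adherence, symptom onset, complications and "Identify the correct frequency regimen of doctors" (that is, how often to attend). Of the three, "the team will choose to simply use 1 scenario in the multicenter multinational cohort trials", and that choice is still to be made.

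**The concern.** The research question, the scenario objectives and the quiz were not built from one another. The question names lifestyle changes, and every candidate scenario has a lifestyle objective. The quiz was drawn from a clinical guideline and is already fixed, although the scenario is not. If the quiz holds no lifestyle content, a difference in score in either direction carries no information on whether patients learned about lifestyle. A report that answered the research question in its stated terms would then claim more than was measured. All three elements are printed in the article, so this is not a detail left to a fuller document.

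**Working it through.** The article gives no figure on this point to reproduce. The check maps items to objectives and weights each item by the article's own scoring rule.

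**Maximum score.** Nine items have four options and one (item 5) has two: 9 × 4 + 2 = 38 points.

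**What each key tests.**

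| Item | Keyed content | Points |
|---|---|---|
| 1 | General facts about AF | 4 |
| 2 | Commonest symptom | 4 |
| 3 | How AF is diagnosed | 4 |
| 4 | Main complication if untreated | 4 |
| 5 | Blood tests under anticoagulants | 2 |
| 6 | Possible admission at diagnosis | 4 |
| 7 | Adherence to the anticoagulant | 4 |
| 8 | Properties of newer anticoagulants | 4 |
| 9 | Anticoagulants in stroke prevention | 4 |
| 10 | Advice on changing from warfarin | 4 |

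**Lifestyle content.** Keys on smoking, alcohol, exercise or diet as a lifestyle change: 0 of 10 items, 0 of 38 points. The nearest content is a rejected option on diet under warfarin (item 10) and a clause on food interactions inside item 8's keyed answer, which describes the drug and not the patient's habits. Counting both in full gives at most 2 items: (4 + 4)/38 = 8/38 = 21%.

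**Overlap with the one scenario used.** Three readings:

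- Strict: the key itself states a Table 1 objective.
- With item 8: also credits its clause on taking the drug every day at fixed times, as adherence.
- Lenient: also credits items 3, 6 and 10 where they touch on seeing a doctor or on diet.

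| Scenario | Strict | With item 8 | Lenient |
|---|---|---|---|
| Chronic AF | item 7: 4/38 = 11% | 7, 8: 8/38 = 21% | 6, 7, 8, 10: 16/38 = 42% |
| Early-onset | 2, 7: 8/38 = 21% | 2, 7, 8: 12/38 = 32% | 2, 3, 6, 7, 8: 20/38 = 53% |
| Lifestyle factors | 4, 7: 8/38 = 21% | 4, 7, 8: 12/38 = 32% | 4, 6, 7, 8, 10: 20/38 = 53% |

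Pooled over all three scenarios, the lenient reading reaches items 2, 3, 4, 6, 7, 8 and 10, or 28/38 = 74%. But patients in the multicentre trial receive one scenario, so the per-scenario rows are the relevant ones.

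The zero for lifestyle does not depend on the mapping rule unless a wrong option or a drug property is counted as lifestyle knowledge. The overlap figures do depend on it.

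**The case against.** The strongest reply is that the question has two parts. Adherence (item 7, in part item 8), symptom recognition (item 2), stroke as a complication (item 4) and anticoagulation can fairly be called needs, and Table 1 lists the first three topics as objectives. The article also states broader aims, and its Discussion puts the focus on knowledge retention. The question does not itself list smoking, diet or exercise; in Table 1, smoking and alcohol appear in a scenario theme and not among its objectives. This stands. A reader might infer that the quiz cannot answer the research question at all. The documents do not support that: it can answer part of it.

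A reader might also infer that most of the score tests what the scenario does not teach, so that a real effect is diluted or the control arm favoured. That cannot be established. No scenario has been chosen, Table 1 is only an outline, the detailed content is still to be written, and patients in the VP arm receive further information after the case questions. The overlap runs from 11% to 53% by reading. A dilution expressed in standard deviations would need assumed success rates and gains that the article does not give.

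For the same reason, the Limitations section cannot be called wrong for describing the quiz as matched to the vignette. The printed items do not demonstrate that match, but the final vignette is not shown. That section also concedes a counterargument, that "we are thus narrowing the evaluation scope to the strong points of our VP resource". A primary score built only from the VP's own objectives would make that objection worse, so it is not a sound remedy here.

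**Conclusion.** The concern holds for the lifestyle part of the research question. Lifestyle change is named in the question and planned in every candidate scenario, but is keyed in 0 of 10 items and 0 of 38 points of the only efficacy instrument named. The trial as printed could support a conclusion on knowledge of AF and anticoagulation, including some patient needs, but not one on lifestyle knowledge. Overlap with the scenario to be used is 1 to 3 items on the stricter readings (11–32% of points) and 4 to 5 on a lenient one (42–53%). These ranges rest on judgement about what counts as a match and on Table 1 as it stands. The group comparison of scores is not invalidated; what it may be said to show is limited.

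**What to change.** Once the scenario is chosen and before the trial starts, add to the existing quiz a few items keyed to that scenario's lifestyle objectives. Confirm that the tested content is in the information given to both arms, so that the new items do not favour the VP arm by design. The present ten items can stay. The cost is writing the items and putting them through the translation and bilingual check already planned. No validation is lost, because the article states that the quiz is not a validated instrument.

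Added items would be a small share of the total. Two four-option items, for example, would give 8/(38 + 8) = 8/46 = 17%. The lifestyle items should therefore also be reported separately if a lifestyle conclusion is wanted.

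Otherwise, restate the research question and the planned conclusion as knowledge of AF and anticoagulation, and drop the lifestyle claim. That costs only a change of wording.
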